# Effects of exercise on secretion transport, inflammation, and quality of life in patients with noncystic fibrosis bronchiectasis

**DOI:** 10.1097/MD.0000000000009768

**Published:** 2018-02-16

**Keywords:** bronchiectasis, clinical trial, exercises, inflammation, mucociliary clearance, rehabilitation

## Abstract

**Background::**

Bronchiectasis is characterized by pathological and irreversible bronchial dilatation caused by the inefficient mucus and microorganism clearance and progression of inflammatory processes. The most frequent characteristic is the increase in bronchial mucus production resulting in slower transport and damage to the mucociliary transport.

**Aims::**

To evaluate the effects of exercise on mucus transport, inflammation, and resistance of the respiratory and autonomic nervous systems and subsequent effects on quality of life in patients with bronchiectasis who are enrolled in a pulmonary rehabilitation program.

**Methods::**

Sixty subjects of both sexes between 18 and 60 years (30 volunteers with clinically stable bronchiectasis and 30 healthy volunteers) will be included. Participants with chronic obstructive pulmonary disease, decompensated cardiovascular or metabolic diseases, neuromuscular and musculoskeletal diseases, and active smokers will be excluded. Volunteers will be randomly allocated to the pulmonary rehabilitation or control groups. The primary outcomes will be nasal transport time as evaluated by nasal saccharin transport time, analysis of nasal lavage, enzyme immunoassay of exhaled expiration, and analysis of the mucus properties. The secondary outcomes will include pulmonary function tests, impulse oscillometry, heart rate variability analysis, and quality of life questionnaires.

**Discussion::**

In addition to the benefits for patients already described in the literature, the additional benefit of mucus removal may contribute to optimizing treatments and better control of the disease.

**Conclusion::**

This protocol could provide new information about the unclear mechanisms regarding exercise to aid in the removal of secretions.

## Introduction

1

Bronchiectasis is characterized by pathological and irreversible bronchial dilatation.^[1,2]^ It is mainly caused by inefficient removal of secretions and microorganisms, as well as the perpetuation of inflammatory processes induced by chronic or recurrent infections. The diagnosis is traditionally performed using high-resolution computed tomography (HRCT) in association with spirometry.^[3,4]^

Spirometry requires great cooperation from subjects. Alternative tests such as impulse oscillometry system (IOS) are suggested for patients who have difficulties in performing the forced manoeuvres.^[5]^ IOS evaluates the impedance of the respiratory system by applying oscillatory pressure waves at multiple frequencies. This technique has been shown to be more sensitive in the identification of airway alterations than spirometry.^[6,7]^ Clinically, the most frequent characteristic is an increase in the production of bronchial secretions. The mucus produced is thicker and results in slower transport, causing damage to the mucociliary transport.^[8]^ Patients may undergo exacerbation periods and acute deterioration of respiratory symptoms related to decreased quality of life, lung function, and increased mortality.^[4]^

The immune response in bronchiectasis is primarily mediated by neutrophils, and increased levels of chemokines and proinflammatory cytokines are found in the airways of affected individuals.^[8]^ High levels of proteases are present at inflammation sites, resulting in the release of proinflammatory cytokines. This causes even more damage to the cells of airway structures.^[9]^ In approximately 50% of cases, there is a diagnosis of a primary disease causing bronchiectasis.^[10]^ Thus, a single clinical or functional parameter is insufficient to assess the severity of the disease. In an attempt to elucidate this problem, Chalmers et al^[11]^ developed the Bronchiectasis Severity Index and concluded that it more accurately stratifies mortality risk, hospital admissions, and future risk of exacerbations. Patients may benefit from specific physiotherapy techniques for the removal of secretions from the respiratory system, as well as overall exercises within pulmonary rehabilitation programs.^[12]^ However, there is little information on the effects of physical training in patients with bronchiectasis.

Several factors induce dysautonomia in patients with bronchiectasis, with probable sympathetic hyperactivation representing an important cardiovascular risk.^[13]^ Impaired gas exchange has been associated with increased sympathetic activation.^[14]^ The autonomic nervous system acts on the mucociliary clearance system, but autonomic nervous system dysfunction in bronchiectasis has been poorly studied. Analyzing heart rate variability may be an excellent measure of autonomic regulation.^[15]^

This study evaluates the effects of exercise on patients with bronchiectasis in a pulmonary rehabilitation program. The considerations include the transport of secretions, inflammation and resistance of the respiratory system, nervous system autonomy, and the repercussions on the quality of life.

## Methods

2

### Ethical approval

2.1

Ethical approval was obtained on March 16, 2016, by the Research Ethics Committee of the Clinical Hospital of the Ribeirão Preto Medical School at the University of São Paulo (2053/2016). The trial has been prospectively registered at ClinicalTrials.gov (NCT02823587). Once patients have accepted an invitation to participate in the trial, their written consent will be obtained before assessing them for eligibility by [name]

### Study design

2.2

The trial is prospective, single-center, parallel, randomized, assessor-blinded trial. This trial will follow the recommendations of the Consolidated Standards of Reporting Trials statement^[16]^ and the Standard Protocol Items for Randomized Trials.^[17]^

### Recruitment organization and randomization

2.3

The volunteers will be recruited in the pulmonology outpatient of Clinical Hospital of the Ribeirão Preto Medical School. A pulmonologist will evaluate HRCT results to determine eligibility. Only volunteers who satisfy all the criteria inclusion will be randomized using simple computerized randomization procedures. After, it will be divided into a pulmonary rehabilitation group and a control group (CG). These groups will be subdivided into a group that will be instructed to follow an exercise protocol and one that will not (Fig. 1). The allocation sequence will be generated by a researcher who is not involved in the assessment and interventions. After allocation to one of the groups, a blind examiner will conduct clinical evaluations and collect data to analyze the primary and secondary variables. Another evaluator will follow the exercise plan. All participants will be assessed at the start of the study after the 8th and 12th weeks. Volunteers may discontinue participation at any time if they wish. However, all efforts will be made to avoid missing data, mainly for the main target criteria, case a patient discontinues the trial, a final visit will be performed, and the data of this visit will be used for the calculation of the main criteria, the primary outcomes. The specific dealing of missing data will be determined in a data review meeting before starting statistical analyses.

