#### Control group (CG)

2.5.2

Participants in the CG will not participate in supervised exercise sessions. They will only be informed at the beginning of the study that performing 30 minutes of moderate-intensity physical activity several days a week is associated with health benefits. During the study, participants in this group will be contacted monthly by phone to provide general support and counseling without discussing exercise or physical activity.

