##### Saccharin transport time

2.6.1.1

It is a nasal technique for to measure mucociliary clearance, widely reported as a simple, non-invasive, valid and reproducible method.^[23]^ The nasal cavity has a respiratory epithelium similar to the rest of the respiratory tract, and nasal mucociliary transport has a good correlation with tracheobronchial transport.^[24]^ Subjects will be seated and positioned with 10 degrees of neck extension. Granulated sodium saccharin (250 μg) will be placed 2 cm inside the right nostril under visual control. The time from particle placement until the first perception of a sweet taste in the mouth will be recorded in minutes by a digital chronometer.

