##### Quality of life evaluation scale

2.6.2.4

The general health status of the patients will be assessed through the Medical Outcomes Study 36-Item Short-Form Health Survey.^[35]^ The quality of life in this group of patients will be evaluated using the Quality of Life in Bronchiectasis Questionnaire^[11]^ and the Leicester Cough Questionnaire to assess the physical, psychological, and social impacts of chronic cough.^[36]^

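### Section 2.3 describes outcome collection only after allocation, and nothing places the baseline before randomization or before participants learn their group

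*Protocol article*

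**What the plan says.** Section 2.1 places written consent before the eligibility assessment. Section 2.3 then has a pulmonologist judge eligibility from the CT scan, and continues: "Only volunteers who satisfy all the criteria inclusion will be randomized using simple computerized randomization procedures". Next comes the division into rehabilitation and control groups, and then "After allocation to one of the groups, a blind examiner will conduct clinical evaluations and collect data to analyze the primary and secondary variables".

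The visit times follow a little later in the same section: "All participants will be assessed at the start of the study after the 8th and 12th weeks". The start of the study is not defined relative to randomization.

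On blinding, section 2.2 says: "The trial is prospective, single-center, parallel, randomized, assessor-blinded trial". No blinding of participants is claimed. The exercise group attends supervised sessions twice a week (section 2.5.1) and the control group attends none (section 2.5.2). For controls, section 2.5.2 adds: "They will only be informed at the beginning of the study that performing 30 minutes of moderate-intensity physical activity" has health benefits. Whether this advice comes before or after the first assessment is not said.

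On the measures, section 2.6.1.1 defines the first-listed primary outcome: "The time from particle placement until the first perception of a sweet taste in the mouth will be recorded in minutes". Section 2.6.2.4 covers the quality-of-life questionnaires, beginning: "The general health status of the patients will be assessed through the Medical Outcomes Study 36-Item Short-Form Health Survey".

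**The concern.** A baseline is a safe reference or covariate because it cannot depend on the assigned group. That protection comes from measuring it before randomization or, failing that, before the participant knows the result. The order in section 2.3 provides neither.

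A blind examiner removes the examiner's expectations, not the participant's. In the saccharin test the examiner times the interval, but the participant decides when it ends. The SF-36, the bronchiectasis quality-of-life questionnaire, the cough questionnaire and the anxiety and depression scale are also the participant's own answers. A participant who has just learned that exercise was, or was not, assigned may answer differently.

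Saccharin time is also the outcome on which the sample size rests (section 2.7). With 15 per subgroup, chance imbalance at baseline can matter, so a clean baseline has practical value. The order of visits is trial conduct, and no analysis can restore it afterwards.

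**Working it through.** **1. The stated order.**

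| Step | Where | Placed relative to randomization |
|---|---|---|
| Consent | 2.1 | before eligibility assessment, so before |
| Eligibility | 2.1, 2.3 | before |
| Randomization and division into groups | 2.3 | – |
| Collection of primary and secondary variables | 2.3 | described as after allocation |
| Start-of-study assessment | 2.3 | not fixed |
| Activity advice to controls | 2.5.2 | not fixed; beginning of study |
| Participants told their group | – | not stated |

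No row puts an outcome measurement before randomization. A baseline after allocation is therefore the natural reading, although no sentence says it outright.

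**2. The planning figures.** Section 2.7 gives a difference of 4 min, SD 3 min, alpha 5% and power 95%. By the two-sided normal approximation:

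n = 2 × (1.960 + 1.645)² × 3² / 4² = 2 × 12.996 × 0.5625 = 14.6, rounded up to 15 per subgroup; 4 × 15 = 60.

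This reproduces the plan's figure. The order of the baseline visit does not enter it.

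**3. How a baseline shift would carry over.** Let one arm's baseline be displaced by b minutes, with follow-up unaffected, no true effect and equal SDs. Let r be the baseline-to-follow-up correlation.

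- Follow-up values only: bias 0.
- Change score: bias b in size; SD of change = 3√(2(1 − r)).
- Baseline-adjusted: bias r × b in size; residual SD = 3√(1 − r²).

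The standard error of each contrast is its SD × √(2/15). For the change score it is 3 × √0.6 × 0.365 = 0.85 min at r = 0.7, and 3 × √1.4 × 0.365 = 1.30 min at r = 0.3.

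**4. Illustration.** The values of b and r are assumptions; the documents supply neither. The entries are rejection rates of a two-sided 5% t test with 15 per group when there is no true effect. The baseline-adjusted figures are approximate.

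| b (min) | Change score, r = 0.3 / 0.5 / 0.7 | Baseline-adjusted, r = 0.3 / 0.5 / 0.7 |
|---|---|---|
| 0.5 | 6.6% / 7.3% / 8.8% | 5.2% / 5.7% / 7.2% |
| 1 | 11.6% / 14.3% / 20.7% | 5.9% / 8.0% / 13.9% |
| 2 | 32.0% / 42.2% / 62.4% | 8.6% / 17.5% / 40.8% |

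**5. The condition on the shift.** If the same displacement b were also present at follow-up, the change-score contrast would be b − b = 0. The table applies only to a shift confined to baseline.

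**The case against.** The sentence about the blind examiner mainly says who collects the data, and it covers every visit. It stands between the sentence on who generates the sequence and the one on who follows the exercise plan. Visit timing is given separately and does not mention randomization. The participant flow diagram (Figure 1) is not shown, and an article may condense the visit schedule. This stands as far as it goes: a post-allocation baseline is the natural reading, not an explicit statement. It does not remove the point, because the only order the text gives leaves the baseline unprotected.

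A reader might infer that participants know their group at baseline. The documents do not say so. Allocation may precede the visit while the participant is still unaware. Nor do they support a claim that people leave one arm before being measured, since both disclosure and dropout before the first visit would have to be assumed.

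A reader might also infer that the treatment comparison is biased by a definite amount. Section 2.8 compares values between groups and mentions neither change scores nor baseline adjustment, and follow-up values alone carry no bias from a baseline shift. Adjustment carries only the fraction r. A reporting shift that persists equally at weeks 8 and 12 cancels in a change score. A shift of 0.5 min would be below one standard error of the change-score contrast (0.85 to 1.30 min). All of this stands.

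Finally, saccharin time is one of several primary outcomes. Cytokines, breath-condensate pH, nitric oxide and mucus transport are measured by instrument or in the laboratory and are much less exposed.

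**Conclusion.** The point holds as a weakness in the stated order, not as demonstrated bias. Section 2.3 describes outcome collection only after allocation, and nothing places the baseline before randomization or disclosure. Because only the assessor is blinded, saccharin time and the self-reported questionnaires could be affected at baseline.

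Harm to the treatment comparison requires three things: participants learn their group before the first assessment, their responses shift differently by arm at baseline but not equally at follow-up, and the analysis uses baseline. The article settles none of them. The size of any shift cannot be derived from the documents, so the error rates above show sensitivity under assumed values and are not estimates for this trial. The change is worth making because the affected outcome drives the sample size and the protection costs almost nothing.

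**What to change.** Reorder section 2.3 as: consent; eligibility; complete baseline assessment of all primary and secondary variables; then randomization and release of the allocation by the independent researcher. Add that participants are not told their group, and receive no group-specific advice (including the activity information for controls in section 2.5.2), until the baseline record is closed. If this is already the practice, the text need only say so.

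The cost is a sentence or two. Visits, staff and the sample size of 15 per subgroup and 60 in total are unchanged. The one downside is that a few participants assessed at baseline may not go on to be randomized. The change protects the baseline only; participants will still know their group at weeks 8 and 12.

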**Figure 1 F1:**
[figure not shown]
Study design. Flow of participants according to the Consolidated Standards of Reporting Trials (CONSORT).

### Study participants and eligibility criteria

2.4

A total of 60 eligible participants with age between 18 and 60 years will be recruited. Of these participants, 30 will have been diagnosed with bronchiectasis that is not attributable to cystic fibrosis and confirmed by HRCT. These subjects will be clinically stable without any evidence of exacerbated bronchiectasis or changes in medical therapy in the previous 4 weeks.^[18]^ Participants will be excluded if they have a smoking history ≥10 pack years, diagnosis of chronic obstructive pulmonary disease,^[19]^ asthma,^[20]^ interstitial lung disease (clinical/radiological diagnosis), and medical conditions that can put the subjects at risk during the exercise protocol (eg, unstable cardiovascular disease) or conditions that may restrict the participant's ability to exercise (eg, severe orthopedic or neurologic impairments). The remaining participants will be 30 nonsmoker volunteers without lung disease and recruited from the community.

### Intervention

2.5

#### Intervention group (pulmonary rehabilitation group)

2.5.1

The intervention group will participate in a supervised exercise program twice a week for 12 weeks. This program will consist of an individual prescription of exercise on a treadmill or bicycle at an initial intensity of 80% of the maximal oxygen consumption (VO_2_ max)^[21]^ obtained from a cardiopulmonary test, as well as active or active-resistance exercises for the upper and lower limbs. The exercises will be performed according to the perception of effort according to the modified Borg scale.^[22]^ Adverse event will be defined as any change in mean arterial blood pressure higher then >140 or less then <65 mm Hg, heart rate <50 or >140 bpm, arrhythmias with hemodynamic consequences, myocardial ischemia, and SpO_2_ <88%. If any adverse event happen, the session will be interrupted the event will be related. A home exercise program will also be prescribed with the goal of achieving 3 to 5 unsupervised sessions per week with the aim of incorporating a regular routine of moderate-intensity physical exercise into the daily lives of the volunteers. The program will consist of 45 minutes of walking (using the Borg scale to reach the desired intensity). This activity will be recorded by a researcher in an individual diary for each volunteer. Participants will be instructed to maintain the exercise routine throughout the study period and will be reminded weekly through telephone calls.

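### A starting load of 80% of VO2 max can collide with the fixed 140 bpm stopping limit: likely for healthy volunteers up to about age 40, not shown for patients

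*Protocol article*

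**What the plan says.** Section 2.5.1 of the protocol article contains both rules.

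- **Dose.** Treadmill or bicycle exercise is prescribed individually "at an initial intensity of 80% of the maximal oxygen consumption", taken from a cardiopulmonary test.
- **Limit.** Adverse events include "heart rate <50 or >140 bpm, arrhythmias with hemodynamic consequences, myocardial ischemia".
- **Consequence.** "If any adverse event happen, the session will be interrupted the event will be related".
- **Adjustment.** "The exercises will be performed according to the perception of effort according to the modified Borg scale". No target score is given.

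The limit is one number for all ages; section 2.4 states: "A total of 60 eligible participants with age between 18 and 60 years will be recruited".

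On who trains, the abstract describes "30 volunteers with clinically stable bronchiectasis and 30 healthy volunteers" and then says: "Volunteers will be randomly allocated to the pulmonary rehabilitation or control groups". Section 2.3 adds: "These groups will be subdivided into a group that will be instructed to follow an exercise protocol and one that will not". Section 2.7 plans 60 volunteers, 15 in each subgroup.

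**The concern.** The dose is scaled to the individual and the ceiling is not. A young, healthy person working at 80% of their own maximum would be expected to pass 140 bpm. For that person the prescription calls for a load that the stopping rule forbids.

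Two things are at stake. Applied literally, the rules stop sessions and record adverse events for an ordinary response to the prescribed load. If staff reduce the load to stay under 140 bpm, the participant does not receive the stated dose. The loss would probably be larger in healthy volunteers than in patients, which matters when the two populations' responses to training are compared.

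**Working it through.** **The plan's own figure.** The article gives no figure linking the two rules. Its only calculated figure is the sample size, which reproduces: with a difference of 4 minutes, SD 3, two-sided 5% and 95% power, the normal formula gives 2 × (1.960 + 1.645)² × 3² / 4² = 14.6, so 15 per subgroup and 4 × 15 = 60. It matters here only because four subgroups of 15 fit two populations each split into exercise and no exercise. That healthy volunteers train is therefore an inference, as Figure 1 is not shown.

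**Inputs from the article.** Intensity 80% of VO2 max; ceiling 140 bpm; ages 18 to 60.

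**Assumptions not in the article.** Peak heart rate is k × (220 − age) with SD 10 bpm, where k = 1 for healthy volunteers and is varied for patients. Heart rate at 80% of VO2 max is a fraction f of peak, with f = 0.80, 0.85 or 0.90. Ages are uniform within each band.

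**Step 1: break-even peak.** Both rules fail together when f × peak > 140, that is, when peak > 140/f:

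- f = 0.80: 175 bpm
- f = 0.85: 164.7 bpm
- f = 0.90: 155.6 bpm

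**Step 2: where the ceiling sits.** 140/(220 − age) is 69.3% of mean peak at age 18, 77.8% at 40 and 87.5% at 60.

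**Step 3: mean expected heart rate, healthy volunteers.** The most lenient mapping, f = 0.80, gives 0.80 × 190 = 152 bpm at age 30, 0.80 × 180 = 144 at age 40, 0.80 × 170 = 136 at age 50 and 0.80 × 160 = 128 at age 60. As a check, 208 − 0.7 × age was also used for peak, and a heart-rate-reserve mapping, rest + 0.8 × (peak − rest) with rest 60-80 bpm. Across these and fixed fractions of 80-88% of peak, the range is 150-168 bpm at age 30, 144-160 at 40, 136-154 at 50 and 128-149 at 60. Every mapping tested exceeds 140 bpm up to about age 40. From about 45-50 the answer depends on the mapping.

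**Step 4: share above 140 bpm.** This is the average over age of P(N(f·k·(220 − age), SD f·10) > 140).

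| Group | f = 0.80 | f = 0.85 | f = 0.90 |
|---|---|---|---|
| Healthy, 18-40 | 91% | 99% | >99% |
| Healthy, 18-60 | 64% | 84% | 95% |
| Healthy, 45-60 | 25% | 60% | 86% |
| Healthy, 55-60 | 11% | 41% | 75% |
| Patients 18-60, k = 0.95 | 43% | 67% | 85% |
| Patients 18-60, k = 0.90 | 22% | 46% | 68% |
| Patients 18-60, k = 0.80 | 1% | 8% | 23% |
| Patients 18-60, k = 0.75 | 0.1% | 1% | 7% |

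For patients aged 45-60 with k = 0.90, the shares fall to 1%, 10% and 33%.

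**The case against.** The strongest reply is that this is an ordinary hierarchy. The stop is unconditional and follows the prescription, so safety overrides load; 80% is only the initial intensity; and the Borg scale lets staff adjust. A cautious fixed ceiling is a legitimate clinical choice. That reading is reasonable, but it does not remove the problem. If the stop prevails, sessions end and a normal response is recorded as an adverse event. If Borg is used to cut the load, the stated dose is not given. The conflict arises at the initial load, so later adjustment comes too late.

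A second reply is that titration and resumption rules belong in the full protocol. That is right, and their absence is not the point. Both rules are stated here, and it is the stated rules that collide.

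Other objections stand:

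- The link between the rules rests on outside assumptions, and the result moves widely with them and with the unreported age distribution. No single percentage describes the trial.
- For patients, the population of main interest, nothing is shown. The Discussion says that their exercise capacity is reduced, and no peak heart rate is given.
- Adverse events are not a listed outcome, so extra records change no planned endpoint.
- The limb exercises and home walking are not prescribed at 80% of VO2 max.

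A reader might infer that the trial cannot deliver its intervention, or that its main result is biased. The documents support neither. The conflict concerns one component of training, its size in patients is unknown, and exercising patients are still compared with randomised controls.

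**Conclusion.** The point holds as a minor one, with medium confidence. If heart rate at 80% of VO2 max is 80-90% of peak, the two rules cannot both be met by anyone whose peak exceeds about 156-175 bpm. Under the assumptions above, that is most healthy volunteers up to about age 40 and a minority to a majority of older ones (11-75% at ages 55-60). For patients it ranges from nearly none to most, depending on a peak heart rate that the article does not report. The healthy-volunteer part also depends on the inference that they train.

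The practical effect is interrupted sessions and adverse-event records for a normal response, or a dose below the one stated, mainly in healthy volunteers. A lower delivered dose would change what the exercise arm received. It would not bias the randomised comparison within patients.

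**What to change.** Amend section 2.5.1 in one of two ways.

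1. Have the clinical team set the upper heart-rate limit relative to each participant's peak on the planned cardiopulmonary test, and above the heart rate recorded there at 80% of VO2 max.
2. If 140 bpm is a deliberate safety ceiling, keep it. State the starting load as 80% of VO2 max or the load that holds heart rate at or below 140 bpm, whichever is lower.

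The cost is an amendment to one paragraph. No new test is needed, assuming that heart rate is recorded during the cardiopulmonary test. The first option permits a higher heart rate for some participants, and the second lowers the stated dose for some. Which is acceptable is a clinical decision that also needs ethics approval.

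### The only adverse event definition is a closed list tied to exercise sessions in the intervention arm; it omits exacerbations, falls and injuries and gives no like-for-like event count across arms

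*Protocol article*

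**What the plan says.** The definition stands in section 2.5.1 of the protocol article, which describes the intervention group. It opens "Adverse event will be defined as any change in mean arterial blood pressure" beyond an upper and a lower limit, and goes on to heart rate limits, "arrhythmias with hemodynamic consequences, myocardial ischemia", and an SpO2 limit. The response follows at once: "If any adverse event happen, the session will be interrupted the event will be related". The last word is most plausibly a slip for reported.

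The same section prescribes two supervised sessions a week for 12 weeks and a home programme "with the goal of achieving 3 to 5 unsupervised sessions per week". A researcher-kept diary covers the home activity, and participants receive weekly reminder calls.

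Section 2.5.2 gives controls no supervised sessions. They are "contacted monthly by phone to provide general support and counseling", and exercise is not to be discussed.

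Section 2.4 requires patients to be "clinically stable without any evidence of exacerbated bronchiectasis" at entry, and without a change in medical therapy, over the preceding four weeks. Section 2.3 places assessments of all participants at baseline, week 8 and week 12. If a patient discontinues, a final visit is held and its data are used for the primary outcomes. Neither the outcome lists in 2.6 nor the analysis in 2.8 mentions adverse events or exacerbations.

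**The concern.** A sentence that says how an adverse event will be defined, followed by a closed list, settles what is counted. This list works as a rule for interrupting exercise. Used as the trial's definition of harm, it has two weaknesses.

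First, it leaves out the events most relevant to this population and intervention: exacerbations of bronchiectasis, and falls or injuries during training. Second, it depends on measurements that belong to an exercise session, and only one arm has supervised sessions. An event count by arm would then largely reflect where measurement took place.

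There is also a consequence for interpretation. The article links exacerbation to worse lung function and quality of life (Introduction) and to retained secretions and inflammation (Discussion). Those are the domains of its outcomes. If exacerbation status at a visit is not noted, a reader of the results cannot tell whether a value was taken in a stable or an unstable patient.

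**Working it through.** The article states no safety figure, so the check is mainly a comparison of the text, with a little arithmetic on scale.

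**Design figure, for context.** Section 2.7 gives a difference of 4 minutes, SD 3 minutes, alpha 5% and power 95%. The two-sided normal approximation is n = 2 × (1.960 + 1.645)² × 3² / 4² = 2 × 12.995 × 0.5625 = 14.6, so 15 per subgroup. This matches the plan; a t test needs 15.65, so 16. The point below does not depend on it.

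**What the definition covers, by setting**

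| Setting | Are the listed limits described as measured? | Would an exacerbation, fall or injury count as worded? |
|---|---|---|
| Intervention, supervised session (2.5.1) | Implied by the interruption rule | Only if it crosses a listed limit |
| Intervention, home session (2.5.1) | Not described; the diary records the activity | No |
| Control (2.5.2) | No supervised session exists | No |
| Weeks 8 and 12, both arms (2.3) | Not described as an adverse event check | No |

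**Share of prescribed sessions that are unsupervised.** The inputs are 2 supervised and "3 to 5 unsupervised sessions per week" at home.
- Lower end: 3 / (3 + 2) = 60%.
- Upper end: 5 / (5 + 2) = 71%.

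These are shares of prescribed sessions, with the home number stated as a goal. They are not shares of events missed.

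**Contact over 12 weeks.** The intervention arm has about 12 weekly calls and 2 × 12 = 24 supervised sessions. At one call every four weeks, controls have 12 / 4 = 3. Spontaneous reports would therefore also be gathered with unequal intensity.

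**Weight of one unstable visit.** With 15 per subgroup, one patient assessed during an exacerbation supplies 1/15 = 6.7% of that subgroup's values at the visit. The article gives no exacerbation rate, so the number of such visits and their effect on any outcome cannot be worked out from it.

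**Stability at entry and afterwards.** Section 2.4 applies a four-week stability condition once. Section 2.3 fixes the later visits without a matching check, and carries a discontinuing patient's final visit into the primary outcomes. No described step marks whether that patient was exacerbating.

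**The case against.** The strongest reply is that this is a condensed journal article. Detailed collection of harms usually sits in the full protocol, which is not shown, and silence here does not prove that nothing is collected. Several stronger readings that a reader might infer fail for this or related reasons.

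- **That control events go uncounted, or are zero by construction.** The article describes no such collection, but calls and visits exist in both arms at which events could be noted.
- **That the list holds only physiological limits and serves only to stop a session.** Two of its items are cardiac events, and the event is also apparently to be reported.
- **That the definition is confined to supervised sessions.** This is an inference from its position and from the interruption rule; the wording does not say so.
- **That no safety comparison is possible.** No between-arm safety analysis is planned in 2.8, so none is defeated.
- **That nothing about clinical state is seen at visits.** A blinded examiner performs clinical evaluations (2.3), and sputum purulence, spirometry and a cough questionnaire are collected (2.6). These are not an exacerbation record, but they are relevant information.
- **That exacerbations contaminate the primary result.** The Discussion cites long-term benefit of rehabilitation on exacerbations, so a difference between arms may be part of the exercise effect.

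All of these qualifications stand. They do not remove the core point. The article does not merely omit a harms section: it states a definition. A fuller document would have to replace that sentence, rather than add detail to it, before an exacerbation or a fall counted as an adverse event.

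**Conclusion.** The point holds in a limited form. The one adverse event definition given is closed, sits in the intervention section and is linked to interrupting a session. As worded it excludes exacerbations, falls and injuries that cross no listed limit, and controls have no session in which the limits would be measured. It therefore gives no like-for-like count across arms. In addition, no described step records exacerbation status at weeks 8 and 12.

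The scale can be described only in terms of exposure: 60% to 71% of prescribed intervention sessions are unsupervised, and none of the control arm's time includes a supervised session. If the four subgroups of 15 are disease status by exercise, the control arm has 30 planned participants, of whom 15 have bronchiectasis and could exacerbate. The effect on any outcome is not quantified, because no event rate is available.

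The conclusion rests on reading the list as complete, which its wording supports, and on the link to exercise sessions, which is inferred from context. It is a modest, inexpensive improvement in how harms are ascertained. It does not show that a planned analysis is invalid, and it takes no position on the listed limits.

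**What to change.** 1. Leave the existing list as a separate session rule. No view is taken on its limits.
2. Add a general adverse event definition that applies to both arms: any untoward medical occurrence after randomisation, expressly including exacerbation or change in medical therapy in the terms already used in section 2.4.
3. Collect it with the same question at the same time points in both arms, namely one monthly call and the week 8 and week 12 visits. Ask it at the final visit of a discontinuing patient too. Keep events volunteered at supervised sessions or weekly reminder calls apart from the count used to compare arms.
4. Report events by arm, and describe exacerbation status at each assessment visit.

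The cost is one added question at contacts already planned and one table. Any analysis that leaves out visits during an exacerbation should be supportive only: it conditions on an event after randomisation that exercise may itself change, and it removes values from subgroups of 15.
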